### Hypotheses

#### Primary hypothesis

In patients with clbp, treatment with BMR+BET will result in a significantly higher increase in functional ability directly at the end, as well as six and twelve months after completion of BMR+BET compared to usual BMR+SET.

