### Sample size and power calculation

Thinking of the short-term effectiveness of both interventions, only small differences between groups and small effect sizes at the end of rehabilitation (t2) (d=0,3 or f(V)=0,15) are expected to be found [12,41,42]. Because of the minor long-term effects of the present usual care, medium effect sizes (d=0,5 or f(V)=0,25) are expected to be found at six and twelve months. This is in line with Friedrich and colleagues [43,44], who were able to show medium effect sizes regarding a reduction of disability when comparing a functional exercise therapy to an exercise therapy which contained additional motivational strategies (Disability Score: d~0,68). Sample power (Software: G-Power 3.0) concerning the primary outcome was approximated for an analysis of covariance at t4 with medium effect size of Cohen’s d=0,5, alpha error 5% and test power of 80%. This approximisation results in a sample size of at least 128 patients without missing values. Anticipating a dropout rate of 40%, it is necessary to include 214 patients (n=107 for each group).

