#### Primary outcome measure

We will use the level of functional limitations associated to clbp twelve months after the end of BMR measured by the Hannover Functional Ability Questionnaire (FFbH-R) as our primary outcome [51]. The FFbH-R consists of twelve items with a three-stage answering scale. Its summary score describes the low back pain associated functional ability in activities of daily living in adults on a scale of 0% (minimum functional ability) to 100% (maximum functional ability). The questionnaire is constructed for response to already light and moderate functional restrictions. The average item intercorrelation amounts to 0.50. The test-retest-reliability with repeated measures after approximately one week is above 0.75, Cronbach alpha figures 0.90 [51]. The one factorial structure of the instrument was confirmed in a principal component analysis. The FFbH-R is comparable to the internationally used Roland Morris Questionnaire for measuring clbp related disability with a correlation of 0.75 [73].

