### Data analysis

Data analysis is carried out following evaluation standards of experimental study designs with control groups, using descriptive methods as well as inferential statistics. An intention-to-treat analysis will be performed. In the case of dropouts and withdrawals, multiple imputation techniques will be used. Baseline differences in demographic as well as the primary and secondary outcomes data will be analysed using two-sample t-tests for parametric and Wilcoxon test for non-parametric distribution as well as Chi-Square test for nominal data. The testing of the hypotheses is conducted via comparison of changes in the intervention and the control group regarding the primary and secondary outcomes. For this purpose, a saturated 4x2-factorial linear mixed effects model in the process of all four assessment time points and two groups as fixed effects and intercept and slope as random effects is used whilst controlling for statistically significant differences at baseline [74]. Changes in outcomes over time are represented by their linear slopes. Because of the disparity between the duration of the inpatient rehabilitation phase (27 days on average) and the follow-up phase (12 months), separate slopes for these phases are estimated by a spline model. Primarily overall group differences are identified by a model comparing likehood ratio test of a hypothesized model incorporating interaction effects of group by time and a nested null model leaving out these interactions. Additionally the slopes of both groups can be compared in two phases whilst controlling for statistically significant differences at baseline. Furthermore, a post hoc analysis using similar mixed effects linear regression techniques is conducted to model effects of secondary outcomes onto the primary outcome to explore possible interactions.

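### The primary question is defined and powered as the 12-month FFbH-R difference, but the hypothesis and the primary test cover all visits, and no 12-month contrast is specified

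*Protocol article*

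**What the plan says.** The protocol article describes its primary question in two ways.

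**Twelve months only.** The Primary outcome measure section specifies: "functional limitations associated to clbp twelve months after the end of BMR measured by the Hannover Functional Ability Questionnaire (FFbH-R) as our primary outcome". Under Sample size and power calculation, power was "approximated for an analysis of covariance at t4 with medium effect size" (d = 0.5, alpha 5%, power 80%). This gives 128 evaluable patients, and 214 after allowing for 40% dropout.

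**All visits.** The Primary hypothesis predicts a "significantly higher increase in functional ability directly at the end, as well as six and twelve months after completion of BMR+BET". The Methods/design paragraph of the Abstract lists all four assessments for the primary outcome. The aims name short-, mid- and long-term effects. The Data analysis section fits a mixed model to all four time points and states: "Primarily overall group differences are identified by a model comparing likehood ratio test of a hypothesized model incorporating interaction effects of group by time". The comparison model omits those interactions. As an addition, group slopes can be compared in two phases, inpatient stay and follow-up. No group contrast at t4 is named.

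The sample size section also gives the expected effects: d = 0.3 at the end of rehabilitation (t2), and d = 0.5 at six months (t3) and twelve months (t4).

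**The concern.** A test that removes all group-by-time terms at once asks whether the groups' courses differ anywhere. It has 3 degrees of freedom in the saturated 4×2 model and 2 in the two-phase spline; the section describes both. A significant result may come from t2 or t3 alone, and so does not show that the declared 12-month outcome differs.

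The phase slopes do not close the gap. The baseline-to-12-month group difference is the inpatient-phase contrast plus the follow-up-phase contrast. Each is a separate comparison, and the sum is not specified as a test.

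Two things are at stake. One is what a significant primary result would let the authors claim about twelve months. The other is whether the stated 80% power describes the test that will be run.

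**Working it through.** **1. The plan's own figure.** Inputs from Sample size and power calculation: d = 0.5 (f = 0.25), alpha 5%, two groups. The ANCOVA F test with 1 numerator df has noncentrality N·f² = 128 × 0.0625 = 8.0. Its power is 0.801 at N = 128 with zero to two covariates, and 0.798 at N = 127. Dropout: 128 / (1 − 0.40) = 213.3, so 214. Both figures reproduce, for a two-sided 1-df test at t4. A one-sided test would need 100 and does not match.

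**2. Set-up for the omnibus test.** From the document: 64 evaluable per arm and effects 0.3 (t2), 0.5 (t3), 0.5 (t4). Assumed, because the document gives no between-visit correlation: common SD of 1, no baseline difference, and correlation ρ from 0.4 to 0.7, either equal between all visits (compound symmetry) or decaying with visit distance (AR(1)). Power comes from the noncentral chi-square distribution at the 5% level, with 3 df (saturated) or 2 df (spline with its knot at the end of rehabilitation).

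For the saturated model under compound symmetry the noncentrality has a closed form:

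λ = (n/2) · Σ(δⱼ − δ̄)² / (1 − ρ), with n = 64 and δ the group differences at t1 to t4.

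**3. Effect at t2 only, δ = (0, 0.3, 0, 0).** The sum of squares is 0.09 − 0.3²/4 = 0.0675. At ρ = 0.5, λ = 32 × 0.0675 / 0.5 = 4.32, and the rejection probability is 0.385. Over ρ = 0.4 to 0.7:

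| Correlation | Saturated, 3 df | Spline, 2 df |
|---|---|---|
| Compound symmetry | 0.33–0.60 | 0.30–0.55 |
| AR(1) | 0.34–0.68 | 0.31–0.60 |

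The overall range is 30% to 68%. A t4 test rejects in 5% of trials in this scenario, since the true t4 difference is zero.

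**4. The plan's expected profile, δ = (0, 0.3, 0.5, 0.5), raw SD scale.** The sum of squares is 0.59 − 1.3²/4 = 0.1675. At ρ = 0.5, λ = 32 × 0.1675 / 0.5 = 10.72, and power is 0.793. Over ρ = 0.4 to 0.7:

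| Correlation | Saturated, 3 df | Spline, 2 df | ANCOVA at t4 |
|---|---|---|---|
| Compound symmetry | 0.71–0.96 | 0.75–0.97 | 0.86–0.98 |
| AR(1) | 0.48–0.68 | 0.51–0.68 | 0.80–0.85 |

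The omnibus test's power runs from about 0.48 to 0.97, on both sides of 0.80. The ANCOVA column starts at 0.80 and rises because d is taken here on the raw SD scale, so baseline adjustment adds power.

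These calculations ignore the planned random slopes and the multiple imputation.

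**The case against.** The strongest reply is that the Primary hypothesis names three follow-up times and the aims cover short to long term, so a test over all visits fits one stated version of the question. That is right, and it makes this an inconsistency within the document, not a stray analysis choice. A reader might infer that long-term benefit is the sole stated aim; the aims section does not say so. Still, an omnibus rejection does not establish superiority at each of the three times, and it leaves the outcome section and the power calculation unmatched.

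A second reply is that the overall test is only a first step and the 12-month effect can be estimated from the same model. It can, but the follow-on comparison is optional and is not the t4 contrast. For the same reason, a reader might infer that the plan declares success with no 12-month effect. It states no such success rule; what stands is that the named primary test can be significant without one.

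Third, a reader might infer that the trial is underpowered. The documents do not support this: the sample size arithmetic is correct, and the omnibus test's power may lie above or below 80%, depending on a correlation they do not give.

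Finally, lack of direction is not a separate fault. A two-sided t4 test also rejects either way, and direction is read from the estimate. The fault is that the omnibus test has no single contrast and no time point.

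An unseen analysis plan does not remove the point, because the article states its primary test affirmatively and that statement conflicts with its own outcome definition.

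**Conclusion.** The point holds as an internal inconsistency over the primary question. The Primary outcome measure and sample size sections fix a 1-df comparison at t4. The Primary hypothesis, Abstract and Data analysis sections spread the question over all visits, and the last decides it with a test that is not the t4 contrast.

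The mismatch follows from the text alone and needs no assumption. Its size does need them: the 30–68% rejection rate with d = 0.3 at t2 and nothing later, and the 0.48–0.97 power under the expected profile, rest on 64 evaluable patients per arm and the assumed correlation structures. The supportable conclusion on power is that 80% was calculated for another test and cannot be carried over; a shortfall is not established. Because it concerns the rule for the main claim, it should be settled before the data are analysed.

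**What to change.** In Data analysis, name as the primary test the 1-df group contrast on FFbH-R at t4, adjusted for baseline FFbH-R, with estimate, 95% confidence interval and a two-sided 5% level. It can be the ANCOVA that was powered or the t4 contrast from the repeated-measures model; either serves. Make the overall likelihood ratio test, the phase slopes and the t2 and t3 contrasts supportive or secondary.

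Reword the Primary hypothesis and the Abstract so that the primary claim is the 12-month difference. A change to the analysis section alone would leave the hypothesis still claiming superiority at three times.

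The cost is rewording only: 128 evaluable and 214 randomised stay as planned, and no further data are needed. The small downside is that the claims at the end of rehabilitation and at six months become secondary.

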### Blinding

Blinding of the therapists is not possible because they will be trained to perform the BET or will be chosen deliver the existing exercise therapy within the BMR during the study period.

Patients will be masked regarding the study group. They will be informed through the staff and in the “informed consent” that the effectiveness of two exercise therapy programs will be compared and that both meet current scientific standards and are appropriate to improve health status. During the study period, patients will be not informed as to whether they participate in the control group or intervention group.

A person who will not be involved in the study process performs the statistical data analysis. Furthermore, the evaluation will be blinded to the treatment group.

### Ethical aspects

Ethical and legal problems are not anticipated because of experiences with comparable studies. This investigation is conducted according to the recommendations of the World Medical Association (Declaration of Helsinki: [75]). Information for the participants and their agreement on study participation is written down as „informed consent“. It is pointed out to the participants that the study participation is voluntary and that they may refuse to participate or to discontinue participation at any time without disadvantages or loss of benefits. According to the national data protection laws all personal data is treated as confidential and is used only for scientific purposes. Ethical approval has been granted by the independent Research Ethics Committee of the Medical Faculty of Friedrich-Alexander-University of Erlangen-Nürnberg (Re.-No. 4510). High ethical demands are also imposed by the study sponsor, the German Pension Insurance Association (Deutsche Rentenversicherung Bund). There is a special focus on data privacy.

## Discussion

In the management of disabling clbp intensive multidisciplinary rehabilitation is recommended. But, the reported effects especially in the long-term are low [8,10]. A traditional approach of exercise therapy which is often deduced from physiological models is a cornerstone within multidisciplinary rehabilitation. With BMR, an intensified and theory-based rehabilitation program with proven short-term effectiveness is available in Germany [12]. Exercise-therapy is a central component within BMR, but in practice a biomedical approach mainly to improve physical fitness has established which might work as an obstacle to enhance the long-term effects of a BMR. However, the growing empirical evidence for the importance of psychosocial factors in the development of clbp [19] and the weak relationship between changes in physical function measures and changes in various health outcomes in clbp after exercise therapy [76] requires a more behavioural approach of exercise therapy to facilitate self-management and adherence to regular physical activity and therefore reducing pain and disability in the long-term [22]. Only two exercise therapy programs with a theory-based and behavioural approach are available for patients with clbp in Germany, both with a focus to enhance exercise adherence [31,32]. The majority of exercise therapy programs in the routine of traditional multidisciplinary inpatient rehabilitation in Germany are not explicitly theory-based, so it is unclear which factors of the chronification process and causal mechanism of clbp are influenced. On the other hand, causal mechanisms remain inadequately clarified, even in theoretical models for clbp [20,77,78]. The evaluation of theory-based exercise therapy programs can contribute to the further development of theoretical assumptions of the chronification process of clbp.

Therefore, there is a need for the development, implementation and evaluation of a theory-based exercise therapy with a behavioural approach (BET) in the context of a BMR. To our knowledge, this is the first RCT to examine the effects of BET for the overall treatment success of BMR in the routine healthcare management of patients with disabling clbp.

Methodological challenges arise from conducting a RCT, which claims a lot of resources, within routine health care in two rehabilitation centres as well as from ensuring high treatment integrity. The latter refers particularly to a potential mixture between the study group and the control group through a communication about intervention contents between patients and therapists within each rehabilitation centre, as well as individual deviations from the treatment protocol. To overcome those potential sources of bias BET is delivered by the same BET-therapist, who will be intensively trained in the use of the program and will receive a detailed trainer manual. BET-therapists will sign a written contract concerning discretion about BET. Regularly, announced visitations during the intervention phase will occur in order to assure adherence to the treatment protocol. Individual deviations from the treatment protocol will be recorded.

Altogether, findings of this study might contribute to a better understanding of the mechanism of action of BMR and the special effects of BET and might be used to improve the quality of these interventions in routine care and therefore reduce the burden to patients with clbp.

## Abbreviations

BMR: Behavioural medical rehabilitation; BET: Behavioural exercise therapy; clbp: Chronic non-specific low back pain; min: Minutes; RCT: Randomised controlled trial; SET: Standard exercise therapy.
